**Study plan**

Women will be screened for eligibility, which will include two screening visits, HIV, and tuberculosis testing, and an HIV clinical evaluation. If a woman has a husband or steady sex partner, he will need to come to the clinic for HIV testing to confirm that he is HIV-infected (and therefore not at risk for HIV infection related to the woman’s study participation) and to provide informed consent, because he may also be exposed to the study product, prior to her enrollment. Informed consent will be obtained. This study includes three study arms: Carraguard, placebo, and a no product arm. During the study, each woman will participate in each study arm, and she will be randomized to one of six study arm sequences (see section 5.5). At the enrollment visit, a pelvic examination will be conducted. During the examination, a baseline cervico-vaginal lavage (CVL) HIV sample and vaginal swab sample will be collected to quantify genital tract HIV, and a baseline colposcopic examination will be conducted to evaluate the mucosal epithelium. After the pelvic examination is conducted, the woman will be randomized to a study arm sequence. When receives a product, she will insert the gel vaginally as directed while still at the clinic. The participant and the research staff will be blinded regarding which gel the participant is using. Fifteen minutes after the product is inserted, a second pelvic examination will be conducted, 2 CVLs and vaginal swab samples will be collected, and a repeat colposcopic examination will be conducted to assess any acute effects of product exposure. If it is determined that one CVL is adequate to assess acute effects, only one CVL will be collected after the gel application at each baseline visit for the duration of the study. Participants who do not use a product will also undergo a second pelvic examination with CVL, vaginal swab and colposcopy at 15 minutes. During each study arm, the participant will use the designated product (or no product) for one week, beginning 3-5 days after the end of her menstrual period. She will have a total of two follow-up visits at day 7 and day 14 (1 and 8 days after discontinuing product use). Women and their partners will be counseled regarding the use of condoms and will be given condoms at no cost, to prevent transmission of different viral strains between partners. Women will be asked to return to the clinic for a pelvic examination with CVL and vaginal swab sample collection for HIV and colposcopy. On day 14 (~7 days after discontinuing product use), another pelvic examination with CVL and vaginal swab for HIV will be conducted. Women will then be asked to wait until 3-5 days after the end of the next menstrual cycle to return to clinic for the first visit in the next arm of their study arm sequence baseline study visit). Data from the baseline study visit will also be used for analysis of day 28 delayed effects or potential carry-over effects from the previous arm. A questionnaire regarding product use, acceptability, and adherence will be administered at the first follow-up visit (day 7) of each product arm. All women will participate in each study arm. The three study visits and data collection described above will be repeated for each of the 3 study arms.

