A pelvic examination will be conducted in which samples for RTI testing and cervico-vaginal HIV viral load will be collected, and colposcopy will be conducted. A rapid semen detection test will be conducted on the CVL to determine if the CVL is contaminated with semen which could effect the HIV viral measurement in the CVL, resulting in an inaccurate measurement of the study participant’s cervico-vaginal HIV viral load. If the CVL is contaminated with semen, this CVL and corresponding swab will be discarded, and the enrollment visit will be rescheduled within 48 hours.

Patients in whom the rapid semen detection test is positive will receive extensive counseling regarding risk of HIV transmission to sex partners and strongly encouraged to use condoms or remain abstinent during the study. Regardless of reported partner status, all study participants will be counseled to use condoms consistently throughout the study.

After the baseline examination and clinical specimen collection, women will be randomized to a study arm sequence. If the first arm of her study sequence is a product arm, she will be given instructions on how to insert the product and, while in the examination room, will vaginally insert the first applicator of gel. She will wait either in the examination room or in the waiting room. After approximately 15 minutes, another pelvic examination will be conducted, cervico-vaginal HIV viral load samples including 2 vaginal swabs and 2 CVL (unless further study indicates that only one is necessary) will be collected, and colposcopy will be done. Neither the woman nor the research team will know which of the two products she is using.

If the first study arm to which the participant is randomized is the arm of the study in which noproduct is used, she will also wait at the clinic for 15 minutes and will have a repeat pelvic examination with cervico-vaginal HIV sample collection and colposcopy.

Women assigned to a product arm will be instructed to insert the gel vaginally once daily for the following 6 days. Women will be given 7 applicators (one extra) to take home.

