## Randomization and dispensing of study products

This study is a cross-over design in which each woman will participate in each of the 3 study arms. Once enrolled in the study, women will be randomized to one of six study arm sequences. Before the study begins, a pseudo-random number generator, available as part of the SPSS software package, will be used to generate a randomization scheme, assigning women to one of the 6 sequences, beginning with Carraguard, placebo, or a no product arm.

Individual envelopes will be prepared for each woman in the study, each containing a unique study identification number. Upon enrollment in the study, each woman will receive the next sequentially numbered envelope. The envelope will contain a code indicating to the study staff her study arm sequence, or the order in which she will participate in each of the three arms: Carraguard, placebo or no product. The study staff will refer to this code when distributing the study products to the participants. Additional participants added to maintain the number of evaluable subjects will be added in groups of six, randomized to one of the six study sequences.

Study gels will be packaged in boxes of eight applicators, with different colored seals indicating Carraguard or placebo. Once randomized, a participant will be considered enrolled in the study and will be included in the intention-to-treat analyses; only women who are started on antiretroviral therapy will be excluded from the intention-to-treat analysis.

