The definition of noncompliance is less than 6 days of study gel use reported at the first follow-up (7 day ) visit. Women who do not meet this criterion will be asked to use gel for up to 3 more days, for a maximum of 6 days. For the analysis, women who use study gel 6 of 9 days or more will be included in the per protocol analysis and those who do not meet this criterion will be included in the intention to treat analysis.

We will have a statistician review the mucosal safety data after the first 25 women have completed the first gel use arm. We will look at the differences in epithelial disruption (includes abrasions, ulcers, and fissures) from baseline to the first follow-up visit (day 7) and compare these differences between the 3 study arms. We will stop enrollment in the study and form a DMC to review the data if there is a difference between groups that is significant at the p<0.001 level, a standard stopping rule for this type of trial (Reference: Geller, N and Pocock, S. Interim Analyses in Randomized Clinical trials: Ramifications and Guidelines for Practitioners. Biometrics 43 1987 213-223).

Study participants will be provided with information regarding how to contact the Chiang Rai Health Center for study results and their blinding code when results are available. Results of the final analysis will be presented to the Chiang Rai Advisory Committee, and at local and international scientific meetings. We also plan to publish the results in the international scientific literature.

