When reporting a serious adverse event to the Population Council study coordinator, the investigator should protect the patient’s confidentiality by excluding names and addresses. The study participant’s unique identification number and enrollment date should be used in the report and the investigator should retain the code to facilitate verification of data by the Population Council study coordinator or drug regulatory authority. The name of the investigator reporting the SAE should be stated. In all cases of SAEs where a relationship with the study product is probably related, study product use should be discontinued immediately. Appropriate treatment should be given.

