# Product interruption criteria

Application of the study product will be interrupted in the following circumstances:

- Pregnancy
- Genital or other major surgery
- Medical condition incompatible with the study protocol or visit schedule
- SAE related to the investigational product
- Consent withdrawn
- Missed follow-up visit. However, at the investigators’ discretion, a participant may resume study participation (after her next menstrual period if menstruating)
- Lack of compliance

If an emergency, such as anaphylactic shock occurs, arises and it is necessary to unblind the product used by a particular participant, four individuals will have access to the randomization scheme, and can be reached both at work and at home, 24 hours a day, at the following telephone numbers:

[name] (NY): work: [contact] home: [contact]

[name] (NY): work: [contact] home: [contact]

[name] (NY): work: [contact] home: [contact]

[name] (Bangkok): work: [name] home: [name] [contact]

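### The response to a p<0.001 epithelial-disruption signal stops new randomisations only; gel arms still ahead of women already randomised are left to discretion until a DMC has been formed and has met

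*Protocol*

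**What the plan says.** Protocol, Data analysis, has a statistician review mucosal safety "after the first 25 women have completed the first gel use arm", comparing the change in epithelial disruption from baseline to day 7 between the three arms. If the difference is significant at p<0.001, the response is: "We will stop enrollment in the study and form a DMC to review the data if there is a difference between groups".

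Four other places decide whom that response reaches.

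- Randomization and dispensing of study products: "Once randomized, a participant will be considered enrolled in the study".
- Study plan: "All women will participate in each study arm". Study arm sequences lists all six orders of Carraguard, placebo and no product.
- Enrollment visit: "Women will be given 7 applicators (one extra) to take home".
- The other routes to stopping gel. Serious adverse events: "In all cases of SAEs where a relationship with the study product is probably related, study product use should be discontinued immediately". Product interruption criteria lists individual circumstances, among them "SAE related to the investigational product". Trial closure considerations gives the sponsor a right to terminate the study for undue risk.

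**The concern.** Stopping enrolment works as a brake when women receive their whole exposure soon after entry. Here a woman's second gel week starts 28 or 56 days after randomisation, so at any look a sizeable group is randomised but not yet exposed to one or both gels. The stated response does not touch that group.

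The DMC is formed only after the trigger, so there is a wait of unknown length. During it, the visit schedule brings women back for their next gel arm unless someone decides otherwise. If the signal reflects harm from one gel, some women would meet that gel for the first time after the trial had seen strong evidence against it. Epithelial disruption is named in Background as a primary and critical endpoint, and ulceration is a listed risk.

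**Working it through.** **1. Which rule covers a randomised woman when the trigger fires?**

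| Section | Scope | Automatic on the trigger? |
|---|---|---|
| Data analysis (interim look) | Women not yet randomised | Yes |
| Serious adverse events | One woman with a probably related SAE | No |
| Product interruption criteria | One woman; a group-level signal is not listed | No |
| Trial closure considerations | Whole study, at the sponsor's choice | No |
| Eligibility criteria; Management of RTIs | Bar visible or persistent disruption at enrolment only | No |

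No row is an automatic hold across randomised women.

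**2. How many women is that?** The protocol gives no figure to reproduce. From the protocol: 60 women, six sequences, about 28 days per arm, 7 days of gel, look at the 25th completed first gel arm. Assumed: uniform accrual over T = 90 to 180 days (Study timeline has enrolment complete in months 4-6), balanced sequences, no dropout, completion read as day 7, and 0-28 days from the 25th completion to the analysis.

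Let r = 60/T women per day.

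- Four of six sequences finish their first gel week at day 7. The two that begin with no product finish it at day 28 + 7 = 35. Mean: (4×7 + 2×35)/6 = 16.33 days. The 25th completion therefore falls at about 25/r + 16.33 days.
- Both gels still to start: one third of women, for their first 28 days, so r × 28/3.
- One gel still to start: the gap between gel starts is 28 days (A-B-C, B-A-C), 56 days (A-C-B, B-C-A) or 28 days (C-B-A, C-A-B). Mean (28 + 56 + 28)/3 = 37.33 days, so r × 37.33.
- Gel starts among randomised women in w days: every woman's second gel plus the first gel of one third, so r × w × 4/3.
- In a gel week at the look: two gel weeks each, so r × 14. The sixth dose falls on day 5, so a share of 5/7 would have fewer than six.

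| Quantity | T = 90 | T = 180 |
|---|---|---|
| r per day | 0.667 | 0.333 |
| Day of 25th completion | 53.8 | 91.3 |
| Randomised by then | 35.9 | 30.4 |
| Both gels to start | 6.2 | 3.1 |
| One gel to start | 24.9 | 12.4 |
| Gel starts in 14 days | 12.4 | 6.2 |
| Gel starts in 28 days | 24.9 | 12.4 |
| In a gel week at the look | 9.3 | 4.7 |
| Of these, under 6 doses | 6.7 | 3.3 |

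A simulation of the same set-up (1500 runs per setting; accrual over 90, 120 or 180 days; 0, 14 or 28 days to analysis) agrees within about one woman: one gel to start 12.7-25.6, both 3.2-6.5, none 5.8-23.8; gel starts 6.3-13.2 in 14 days, of which Carraguard 3.1-6.6, and 12.8-25.6 in 28 days, of which Carraguard 6.4-12.8. Counting arms not yet finished instead of not yet started, about 12-25 women have one outstanding and 5-11 have both.

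**3. What does the enrolment stop itself protect?** With T = 90 and 28 days to analysis, 0.667 × (53.8 + 28) = 54.6 women are randomised. The stop then protects about 5, while 24.9 + 6.2 = 31.1 randomised women have a gel still to start. With T = 180 and no delay, the stop protects 60 − 30.4 = 29.6, against 12.4 + 3.1 = 15.5.

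**4. How strong is the trigger?** The test is not named. As an illustration, Fisher's exact test on an assumed 13 v 12 split of the two gels gives (715 + 220)/2,042,975 = 0.00046 for 9/13 v 0/12, and (1287 + 495)/1,081,575 = 0.0016 for 8/13 v 0/12. The rule fires only on a very large difference.

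**The case against.** The strongest reply is that this argues from silence. Both stated actions are sensible, and nothing tells staff to keep dispensing. A reader might infer that the protocol requires dosing to continue, or that nobody could stop it. The documents support neither. The sponsor may terminate for undue risk, Protocol amendments lets IRB chairs approve changes that do not increase risk ahead of a full meeting, and the DMC, once formed, could recommend a stop. What remains is that these routes are discretionary and none is tied to the trigger.

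The consequence is also limited. Related gels caused no significant irritation in Phase I, and interim reviews of Carraguard in HIV-negative women led to no change. Each gel arm has examinations before gel, at 15 minutes and at day 7, and any abnormality found is an adverse event. This reduces the risk to each woman, but no product hold is attached to what the examinations find.

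A reader might also take every gel start during the wait as an exposure to harm. If one gel is responsible, only about half are: roughly 3-7 women in 14 days or 6-13 in 28.

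Finally, the trigger states no direction. An unconditional hold could follow a difference in which a gel arm showed less disruption than no product. That objection stands, and the fix is limited accordingly.

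**Conclusion.** The point holds as a response badly matched to a cross-over, not as a contradiction or as an instruction to keep dosing. Followed as written, the rule protects women not yet randomised and leaves those already randomised to individual or sponsor discretion until a committee that does not yet exist has met.

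The textual finding needs no assumption. The counts do: they rest on uniform accrual over 3-6 months, 28-day arms, no dropout and an assumed 14-28 day wait for the DMC, and they show scale only. In every setting tried, more women had one gel arm outstanding than both. The trigger may well never fire. The change is worth making because it is cheap and concerns the mucosal safety of women already in the trial.

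**What to change.** Add to Data analysis and to Product interruption criteria: if the p<0.001 trigger reflects more disruption on a gel arm than on a comparison arm, the following are held for all randomised women until the DMC has reviewed the data: dispensing of the implicated gel, the start of any new arm with it, and use of its applicators already taken home. Hold both gels if holding one would break the blind; this needs thought because the boxes carry differently coloured seals. Identify the DMC members before the first randomisation so that they can meet at once. State how gel weeks cut short by a hold enter the day-7 and per-protocol analyses.

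The cost is a few sentences and the early naming of a committee the protocol already foresees. The rest arises only on a trigger:

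- If both gels are held, about 3-7 women in mid-gel-week would have fewer than six doses. They would miss the rule that "women who use study gel 6 of 9 days or more will be included in the per protocol analysis", and their day-7 shedding outcome would be affected.
- Later arms are delayed and washouts lengthen. Follow-up visits lets a woman start her next arm a month late, but does not provide for an open-ended hold of everyone.
- A 28-day hold takes a woman to 3 × 28 + 28 = 112 days from enrolment, or 30 + 112 = 142 days from first screening. Eligibility asks for a planned stay of at least four months, so some women may leave before finishing.

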## Study timeline

Month 1-3: Training and begin enrollment

Month 4-6: Complete enrollment

Month 7-9: Complete follow-up

Month 10-12: Complete analysis

Start date: March 2003

## Training

Several weeks before beginning study enrollment, additional training will be conducted on the study procedure with the study staff in Chiang Rai.

# Human subjects review, informed consent, and confidentiality

The protocol requires that written informed consent be obtained for all study participants. The readability of the written informed consent forms will not exceed the 8th grade level. The consent forms will be translated into easy-to-read Thai language versions, and the translation will be verified by blinded back translation. The enrollment consent form will be reviewed with the Chiang Rai Microbicide Research Community Advisory Group (see Introduction). A dedicated study research nurse will be present and will explain the informed consent form to each woman at the time of enrollment. The protocol must be approved by all Institutional Review Boards (the Population Council IRB, the U.S. CDC IRB, and the Thai Ministry of Public Health Ethical Review Committee) before the first study participant is screened.

Women will be informed that they are completely free to refuse participation or to withdraw from the study anytime after enrollment, without consequence to their medical care. Investigators will provide confidentiality for participants, to the extent allowable by law, and their names will not appear on study forms. All laboratory specimens, evaluation forms and records will be identified only by a coded number to maintain participant confidentiality. All records will be kept in a locked filing cabinet at each study site. Data will be electronically transmitted only in a form that cannot be identified with the participant. Only the study staff will have access to a separate file where participant names are linked to identification numbers. Clinical information will not be released without the permission of the participant, except as required for monitoring by the study sponsor (The Population Council). National and international regulatory agencies may also request access to records, including medical record, but the identity of individual participants will remain confidential in such instances.

Each potential study participant will sign an informed consent for screening (Appendix 1) prior to the screening on Day -30. Signed informed consent will also be required from study participant husbands/steady partners (Appendix 2) at the first baseline visit (enrollment). Women who are eligible and who choose to participate in the study will sign an informed consent for enrollment (Appendix 3) at the first baseline visit (enrollment). The informed consent forms will be filed in a locked filing cabinet at the study clinic or the TUC Chiang Rai office with the Study Participant Identification Register. Keys will be available only to study staff.

As part of the Population Council’s monitoring responsibilities, the participant will be asked to acknowledge that an interview may be requested by a representative of the Population Council to determine whether informed consent was given. If an interview is requested, the participant will have the option of accepting or declining the interview.

All participants will be given the name and telephone number of the local study coordinator for any questions about the study or problems during the study, including if she feels that she is experiencing side effects or complications of the study products. All participants will be given the name and telephone number of an independent source of information (a nurse in the clinic not associated with the study) if there are questions about the way in which the study is being conducted. All participants will be given the name and telephone number of a Ministry of Public Health Ethical Review Committee official for use if there are questions about the rights of a study subject.

# Adverse events

Any untoward medical occurrence in a participant during the trial should be reported as an adverse event (AE), whether or not there is a relationship with the study product. Investigators should rate the adverse event as Aunrelated,” “possibly related,” or Aprobably related” to the study product, as shown on the adverse event forms. Therefore, all reproductive tract infections, (except HPV), including asymptomatic infections and HIV infection, all abnormal laboratory results, any abnormality detected during the gynecological/visual examination, and discomfort (including painful sexual intercourse and painful urination), should be considered an adverse event. A recurrence of signs, symptoms or infections reported as adverse events on previous forms, but for which adequate treatment was given, should be considered as new adverse events.

